### Sample size

Sample size calculations were based on scabies prevalence in Western Province of Solomon Islands and the effect size measured in previous studies of ivermectin-based MDA for scabies.^6 17 21^ A standard Monte Carlo simulation method with 1000 repetitions was used to estimate the required sample size and number of villages to achieve statistical power of 80%.^49^ We assumed that scabies prevalence across villages would range from 10% to 30% (mean 20%, SD 5%) at baseline.^6^ The effect size measured in previous studies with two doses of ivermectin MDA was used to assume the prevalence of scabies 12 months after MDA will be between 3% and 9% (mean 6%, SD 2%) in the one-dose group and between 1% and 5% (mean 3%, SD 1%) in the two-dose group.^17 21^ We assumed an average village size of 250 people, with a range of 200 to 300.^50^ We considered a non-inferiority margin of 5% (prevalence of scabies at 12 months in the one-dose group minus prevalence at 12 months in the two-dose group) to be relevant from a public health perspective. Based on these assumptions, 20 villages, randomised equally, would be sufficient to achieve the required power.

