**Trial registration details:**

Australian New Zealand Clinical Trials Registry: ACTRN12618001086257. Date registered: 28 June 2018.

Strengths and limitations of this studyThe cluster-randomised study design follows the implementation of the intervention at a village levelFollow-up at both 12 and 24 months will demonstrate longer term effects of the interventionThe sample size (5000 people across 20 villages) achieves a statistical power of 80%This study is being conducted in partnership with the Solomon Islands Ministry of Health and Medical Service in a culturally sensitive manner and will build the capacity of local nursing staffScabies prevalence is high in the isolated island villages where this study will be conducted (approximately 20%), therefore results may not be transferable to lower prevalence or urban settings

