### Randomisation

An independent statistician will randomise villages to the one-dose or two-dose group in a 1:1 ratio once the 20 study villages have agreed to participate. There will be no stratification within the randomisation process. There will be 10 villages in each group (figure 3).

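### The stated 80% power belongs to the difference in 12-month prevalence; for the change-from-baseline comparison set as the primary analysis, the plan's own SDs give about 11–24%

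*Protocol article*

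**What the plan says.** The protocol article (Sample size) reports a Monte Carlo simulation used to "estimate the required sample size and number of villages to achieve statistical power of 80" per cent. Its inputs are:

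- baseline: "scabies prevalence across villages would range from 10% to 30% (mean 20%, SD 5%) at baseline"
- 12 months, one dose: "between 3% and 9% (mean 6%, SD 2%) in the one-dose group"
- 12 months, two doses: "between 1% and 5% (mean 3%, SD 1%) in the two-dose group"
- an average of 250 people per village, range 200 to 300
- a 5-point margin, defined as 12-month prevalence with one dose minus 12-month prevalence with two

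It concludes: "Based on these assumptions, 20 villages, randomised equally, would be sufficient to achieve the required power". The strengths and limitations list repeats the claim: "sample size (5000 people across 20 villages) achieves a statistical power of 80" per cent. Under Randomisation: "There will be 10 villages in each group".

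The Primary outcome section of the Analysis plan describes another statistic. Each village's difference between baseline and 12 months is computed, these differences are averaged within arms, and the arm means are compared. One dose is non-inferior if the upper limit of the two-sided 95% CI does not exceed 5%. The Analysis plan works on cluster-level summaries throughout.

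**The concern.** With equal expected baselines, the change comparison and the 12-month comparison target the same 3-point difference, so a 5-point margin can be applied to either. Their precision is very different. The change score brings in a baseline spread of 5 points, against 2 and 1 at 12 months, and the power statement does not say which statistic was simulated.

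The risk lies in interpreting a miss. The Discussion says that a finding against one dose would bear on scabies control strategy. A reader who believes the trial had 80% power would take a failure to show non-inferiority as evidence against one dose. If the prescribed analysis has 11–24% power, such a failure is expected in 76–89% of trials even when the planning scenario is exactly true. The false-positive rate is not affected; a positive conclusion would keep its stated protection.

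**Working it through.** **Inputs.** From Sample size: true difference 6 − 3 = 3 points, margin 5, so the gap to the margin is 2 points; SDs 5 (baseline), 2 and 1 (12 months); 250 people per village. From Randomisation: 10 villages per arm. From Primary outcome: two-sided 95% CI, so 1.96, or t on 18 degrees of freedom = 2.101. The baseline/12-month correlation ρ is not given, so I use 0 to 1. Change is read as 12 months minus baseline, so that positive values count against one dose.

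**Step 1: reproduce the plan's figure (12-month difference, SDs taken as total).**
- SE = √((2² + 1²)/10) = 0.707.
- Power = Φ(2/0.707 − 1.96) = Φ(0.87) = 80.7%. With t on 18 df it is 76%.
- Villages per arm for 80%: (1.96 + 0.842)² × 5/2² = 9.8, so 10.

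The stated power and the stated number of villages both come out.

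**Step 2: the same comparison with sampling error added to the SDs.**
- Binomial variances in squared percentage points: 0.06 × 0.94/250 gives 2.26; 0.03 × 0.97/250 gives 1.16.
- SE = √((4 + 1 + 2.26 + 1.16)/10) = 0.918.
- Power is 59% (normal) or 54% (t). Simulation with villages truncated to the stated ranges gives about 65% (t) to 70% (normal).
- About 17 (normal) or 18 (t) villages per arm would be needed for 80%.

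**Step 3: the change from baseline, as the Primary outcome section prescribes.**
- Variance of a village change without sampling error: one dose 25 + 4 − 20ρ; two doses 25 + 1 − 10ρ; sum 55 − 30ρ.
- Sampling error adds 2 × 6.4 (baseline, 0.20 × 0.80/250 per arm) + 2.26 + 1.16 = 16.22.
- SE = √(sum/10).

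| ρ | SE, no sampling error | Power, normal / t | SE, with sampling error | Power, normal / t |
|---|---|---|---|---|
| 0 | 2.35 | 13.4% / 12.5% | 2.67 | 11.3% / 10.6% |
| 0.5 | 2.00 | 16.9% / 15.6% | 2.37 | 13.2% / 12.3% |
| 1 | 1.58 | 24.4% / 22.3% | 2.03 | 16.5% / 15.2% |

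The range is therefore about 11–24%. The CI half-width under t would be 2.101 × 1.58 = 3.3 to 2.101 × 2.67 = 5.6 points, against a gap of 2. Reaching 80% would take 50 to 108 villages per arm without sampling error and 81 to 140 with it (normal quantile).

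**Step 4: can a favourable correlation rescue the change score?** No. Even at ρ = 1 the SD of a village change is 5 − 2 = 3 (one dose) and 5 − 1 = 4 (two doses), above the 12-month SDs of 2 and 1. Under these inputs, subtracting baseline always loses precision.

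**The case against.** The strongest reply is that the 80% is not miscalculated: Step 1 recovers both the power and the 10 villages per arm, on the scale on which the margin is defined. That stands.

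It also rules out a stronger reading that a reader might infer from Step 2, namely that the plan's own assumptions yield only 54–65% for the 12-month comparison. That holds only if 2% and 1% are spreads of true village prevalence, with sampling error to be added. The article does not say so, and the Primary outcome section defines village prevalence as an observed proportion. Nor is the sampling-error model the only alternative: truncating to the stated ranges with no sampling error gives 94%, although truncation shrinks the SDs to about 1.5 and 0.9, contrary to the stated values.

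Two things do tell against the total-SD reading. At 3% prevalence and 250 people the binomial SD alone is √(0.03 × 0.97/250) = 1.08 points, already above the stated 1. And village size, a listed input, plays no part in Step 1. So that reading is optimistic, but it is not shown to be wrong.

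It may also be said that an article leaves simulation detail to the full protocol or analysis plan. That is fair for the sampling model taken alone. It does not cover the mismatch, because the article itself states both the power and the primary statistic.

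**Conclusion.** The 80% in the Sample size section and in the strengths list does not apply to the analysis in the Primary outcome section. It is recovered at the stated SDs for the 12-month difference, with a normal quantile and SDs that already contain sampling error; a t quantile gives 76%. For the prescribed change score, power is about 11–24%. That range rests on the stated SDs, 10 villages per arm, a true difference of 3 points and a non-negative correlation, and no correlation or sampling model within it comes near 80%. If the baseline spread between villages were well below 5 points, the change score would do better; the article reports no observed value.

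The size of any shortfall for the 12-month comparison stays conditional: about 54–59%, or 65–70% with truncation, if sampling error must be added. The documents do not establish that it must.

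**What to change.** Reconcile the Sample size and Primary outcome sections. Make the primary comparison the between-arm difference in 12-month village prevalence, one dose minus two doses, tested against the 5-point margin. Preferably adjust it for baseline village prevalence by cluster-level ANCOVA, which keeps the estimate on the scale of the margin and uses baseline only as far as it predicts outcome.

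Restate the power in the Sample size section and the strengths list for that analysis, with a t quantile and a named sampling model: about 76% if the SDs are total, about 54–65% if sampling error is added, before any gain from baseline adjustment. That gain depends on the unstated correlation. If the change score is kept, give its power as about 11–24%.

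Do not enlarge the trial. The cost is a short simulation, edits to the power statements and the primary analysis paragraph, and a less favourable published figure. Trial status places the 12-month survey in May to July 2020, just before publication, so the amendment should be dated and should state whether 12-month results by arm had been seen.

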### Randomisation

An independent statistician will randomise villages to the one-dose or two-dose group in a 1:1 ratio once the 20 study villages have agreed to participate. There will be no stratification within the randomisation process. There will be 10 villages in each group (figure 3).

**Figure 3 F3:**
[figure not shown]
Study flow diagram. approx., approximately; MDA, mass drug administration

### Analysis plan

We will account for clustering when calculating all study outcomes by calculating outcomes at the cluster level, and analysing data at the cluster level and not the individual level.^51^ The range of cluster-level outcomes will be reported by group.

#### Primary outcome

The prevalence of scabies in each village will be calculated at baseline (0 months) and at 12 months. The prevalence will be calculated by dividing the number of participants with scabies by the denominator (the total number of participants examined for scabies) in each cluster. The denominator will vary at each time point as we will include all participants who consented for skin examination, regardless of their involvement at other time points.

The difference in scabies prevalence between baseline and 12 months will be calculated for each village. The means of these differences will be calculated in the two treatment groups and compared by calculating the difference between the means. If the upper limit of the two-sided 95% CI of the mean difference between the two study groups is less than or equal to 5% (the clinically relevant non-inferiority margin) the one-dose regimen will be considered non-inferior.

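### The 5-point margin is defined on 12-month prevalence but tested on unadjusted change from baseline, which on the plan's own assumptions has about 11–22% power, not 80%

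*Protocol article*

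**What the plan says.** All references are to the protocol article.

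- **Sample size.** The margin is 5%, and its scale is spelled out: "prevalence of scabies at 12 months in the one-dose group minus prevalence at 12 months in the two-dose group". A Monte Carlo simulation was used to "estimate the required sample size and number of villages to achieve statistical power of 80" percent. For the starting point, "We assumed that scabies prevalence across villages would range from 10% to 30% (mean 20%, SD 5%) at baseline". The assumed 12-month village prevalence is mean 6%, SD 2% with one dose and mean 3%, SD 1% with two doses. Villages average 250 people.
- **Primary outcome.** "The difference in scabies prevalence between baseline and 12 months will be calculated for each village". The arm means of these village differences are compared, and the decision rule reads "If the upper limit of the two-sided 95% CI of the mean difference between the two study groups is less than or equal to 5" percent. No adjustment for baseline is described.
- **Randomisation.** "There will be 10 villages in each group", without stratification.
- **Secondary outcomes.** Scabies at 24 months and impetigo at 12 and 24 months follow the same method.

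**The concern.** The margin belongs to one contrast and the test is carried out on another. The change score carries the between-village spread at baseline (SD 5 points), which is much larger than the spread expected at 12 months (SD 1–2 points). Most of the variance of the primary statistic would then come from where villages started, not from what the regimens did.

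Two things are at stake. First, if the planned effect is true, the trial may have little chance of showing non-inferiority under its own rule. Second, any chance difference in baseline prevalence between two unstratified sets of 10 villages passes in full into the primary estimate.

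**Working it through.** **Inputs (Sample size, Randomisation, Primary outcome).** Margin 5; true difference 6 − 3 = 3; distance to the margin 2 points; 10 villages per arm; two-sided 95% CI. Village SDs: baseline 5, 12-month 2 (one dose) and 1 (two doses). The baseline/12-month correlation r is not given, so the full range 0 to 1 is shown. The sign is taken so that a positive contrast means higher prevalence, or less reduction, with one dose.

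**Formula.** By normal approximation, power = Φ(2/SE − 1.96). The t version uses the noncentral t with 18 df.

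**1. Reproducing the plan's figure on 12-month prevalence.** SE = √((2² + 1²)/10) = 0.71. Power = Φ(2/0.707 − 1.96) = 80.7%, or 76% by t. The normal approximation requires exactly 10 villages per arm.

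**2. The analysis as written.** The variance of a village change is 25 + s² − 2·r·5·s, with s = 2 or 1.
- r = 0: 29 + 26 = 55
- r = 0.5: 19 + 21 = 40
- r = 1: 9 + 16 = 25

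SE = √(sum/10).

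**3. Adding binomial sampling.** If the stated SDs describe true prevalences, sampling 250 people per village adds variance in squared points:
- baseline, each arm: 20 × 80/250 = 6.40
- 12 months, one dose: 6 × 94/250 = 2.26
- 12 months, two doses: 3 × 97/250 = 1.16

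For the change scores this adds 2 × 6.40 + 2.26 + 1.16 = 16.22 to the sum.

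| Analysis | SE, SDs as stated | Power z / t | SE, sampling added | Power z / t |
|---|---|---|---|---|
| 12-month difference | 0.71 | 80.7% / 76% | 0.92 | 59% / 54% |
| Change, r = 0 | 2.35 | 13.4% / 12.5% | 2.67 | 11.3% / 10.6% |
| Change, r = 0.5 | 2.00 | 16.9% / 15.6% | 2.37 | 13.2% / 12.3% |
| Change, r = 1 | 1.58 | 24.4% / 22.3% | 2.03 | 16.5% / 15.2% |

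**4. Can another convention recover 80%?** Without sampling error, a one-sided 5% level gives 21–35%. Truncating the distributions at the stated ranges gives at most about 30% (normal approximation, r = 1). At 80% power and with no sampling error, change scores would need about 108, 79 or 50 villages per arm for r = 0, 0.5 or 1.

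**5. Why subtracting baseline hurts here.** A change score forces a slope of 1 on baseline. The slope implied by the stated SDs is r·s/5, at most 2/5 = 0.4 with one dose and 1/5 = 0.2 with two. The variance added by subtracting baseline is 25 − 10·r·s, which is at least 5 (one dose) and 15 (two doses) even at r = 1. So the change score is less precise than the plain 12-month comparison at every correlation.

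**6. Chance imbalance.** The SD of the difference in mean baseline prevalence between arms is 5 × √(2/10) = 2.2 points, against a 5-point margin.

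**7. Baseline-adjusted regression (simulated, 17 df).** Power for r = 0, 0.5 and 0.9 is about 74%, 84% and over 99% with the SDs as stated, and about 53%, 57% and 69% with sampling added.

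**The case against.** The strongest reply is that randomisation gives both contrasts the same expected value (3 points under the planned effect), so the change score is unbiased and its overall type I error is near 2.5%. That stands. A reader might infer that the margin is invalid for the tested quantity or that the test is biased; the documents do not support either. Error rates conditional on one arm starting higher are worse, but they are offset when the imbalance runs the other way.

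Second, the document does not say which statistic was simulated. It lists the baseline distribution among the inputs, which a comparison of 12-month prevalence alone would not need, and village size, which matters only if sampling was simulated. This also stands: that the 80% was computed on the 12-month difference is inferred from its reproduction there. It does not rescue the plan, because if change scores were simulated, no correlation yields 80%.

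Third, one might argue that the effect is proportional, so that high-prevalence villages fall further and the change score over-corrects. The reduction of around 90% cited in the article is a population-level result of earlier studies; the plan's own means imply 70% (20 to 6) and 85% (20 to 3), and nothing is said about individual villages. The argument is not needed, since the slope bound in step 5 holds for any correlation.

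Fourth, the low power applies to the planned 3-point difference. If the regimens were truly equal, change scores would show non-inferiority more often: by t, about 52–85% with the SDs as stated and 43–64% with sampling added. So it would overstate the case to say that failure is almost certain or that the regimen plays no part in the result.

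**Conclusion.** The point holds as a mismatch that costs precision. The margin is explicitly on 12-month prevalence, and the primary test is explicitly on unadjusted change. On the plan's own means and SDs the written analysis has about 11–22% power (t, r from 0 to 1, with or without sampling error) and would miss the planned effect about 78–89% of the time. Either the analysis or the stated 80% has to change.

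The size rests on the baseline SD of 5 points and the 12-month SDs of 2 and 1 points holding in the trial. The correlation and the status of the SDs (with or without sampling error) are not given, so they are covered by ranges. A reader might also infer that switching analysis restores 80%; that is not assured, because if the SDs exclude sampling error even the 12-month comparison has only about 54% power by t.

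**What to change.** By a dated amendment before the 12-month data are analysed:

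- Make the primary analysis a village-level linear regression of 12-month prevalence on arm and baseline village prevalence (ANCOVA, t with 17 df). Declare one dose non-inferior if the upper 95% limit for one-dose minus two-dose is at most 5 points.
- Keep the change-score comparison as descriptive only.
- Use the same model for scabies at 24 months and impetigo at 12 and 24 months.
- Restate the power for the chosen analysis, saying which statistic was simulated, what correlation was assumed and whether the village SDs include sampling error.

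The cost is one degree of freedom and the amendment itself; baseline prevalence is already collected. At r = 0 the adjustment costs slightly more than it gains (about 74% against 76% for the unadjusted 12-month comparison); it gains clearly at r = 0.5 and above. Because the trial is open-label and baseline collection is complete, the baseline imbalance can already be known, so the amendment should record its date, its reason and what had been seen when the choice was made.

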#### Secondary outcomes

The analysis for the prevalence of scabies at 24 months and impetigo at 12 and 24 months will be done in the same way as for the primary endpoint.

The change in the number of presentations to health facilities for scabies and impetigo will be analysed in three ways. First, the total number of presentations in the 12 months before MDA will be compared with the number of presentations in months 1 to 12 and 13 to 24 after MDA. Second, we will calculate the proportion of clinic presentations for scabies and impetigo by dividing the number of presentations for scabies and impetigo by the total number of clinic presentations for any condition. We will calculate this proportion for the 12 months before MDA, 1 to 12, and 13 to 24 months after MDA. Calculating the proportion will account for any changes in population size or operational status of health facilities. Third, we will compare the number of clinic presentations for scabies and impetigo in the clinics that service the study villages and compare this with clinic presentation for scabies and impetigo in other clinics in the province, this will be adjusted for population size.

The number of adverse events in each study group will be calculated as a proportion of the total number of participants in each study group that received MDA at baseline. We will also report the number of deaths in the month following MDA in each study group as a proportion of the number of participants in each group.

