## Discussion

Scabies is a common disease in many tropical and low-income settings and has been prioritised for control by WHO, but there are still gaps in knowledge to determine the optimum approach to control in settings where scabies is highly endemic.^9^ The results of this trial will have an impact on national, regional and global strategies for scabies control.

Island communities in the Pacific have among the highest global prevalence of scabies and understanding how to implement MDA in these settings has the potential for translation into huge public health impact for these communities.^5^ However, the results may not be generalisable to populations with a much lower prevalence of the disease, to settings with higher population density or to urban settings. The non-inferiority margin of 5% was determined using available evidence but may not represent the appropriate level of public health significance in all circumstances. A greater or lesser margin may be considered non-inferior in other settings, depending on factors, including baseline disease prevalence, number of rounds planned, costs of implementing each regimen and available resources. This trial is designed to assess a single round of MDA, there is scope for further research to assess the efficacy of repeated annual rounds of MDA. The cluster-randomised design will allow analysis of the impact of MDA at the community level. We will be able to assess the impact of the intervention on the whole community, even for those who will not receive MDA.

If the RISE trial finds that one-dose ivermectin MDA is inferior, then the need for two doses of ivermectin-based MDA would need to be taken into account in decision-making around control strategies for scabies. It would also provide impetus for further research to identify new treatments for scabies that may be able to be implemented with one dose. Approaches may include novel treatments that are ovicidal or other medications with a longer half-life such as moxidectin.^57^ If one-dose ivermectin-based MDA is found to be non-inferior to two-dose, then this strategy will be highly attractive for implementation as a public health programme. The lower cost, simplified logistics and ability to integrate with other programmes would make scabies control programmes more feasible in low-income settings.

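### Read literally, the 5-point non-inferiority rule and the unadjusted change score extend to impetigo and to 24 months, although the margin was set only for scabies at 12 months

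*Protocol article*

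**What the plan says.** The Secondary outcomes section states: "The analysis for the prevalence of scabies at 24 months and impetigo at 12 and 24 months will be done in the same way". The comparison is with the primary endpoint, and the section adds no exception and no separate margin.

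The Primary outcome section sets out that way in sequence:
- The unit of analysis is the village change: "The difference in scabies prevalence between baseline and 12 months will be calculated for each village".
- The mean change is compared between groups, with no adjustment for baseline.
- A decision follows. It looks at the upper two-sided 95% confidence limit for the between-group difference, and the criterion reads: "less than or equal to 5% (the clinically relevant non-inferiority margin) the one-dose regimen will be considered non-inferior".

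The Sample size section defines the margin as "prevalence of scabies at 12 months in the one-dose group minus prevalence at 12 months in the two-dose group". The prevalences and SDs given there are for scabies only: 20% (SD 5%) at baseline, then 6% (SD 2%) with one dose and 3% (SD 1%) with two doses at 12 months.

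Table 1 and the Aims section use non-inferiority only for the primary objective. The secondary objectives are worded as impact.

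**The concern.** A margin has meaning only in relation to the outcome it was set for. Taken at its word, the Secondary outcomes sentence produces up to three further non-inferiority decisions: impetigo at 12 months, impetigo at 24 months and scabies at 24 months. The 5 points were set for none of these. The objectives point the other way, so a reader cannot tell whether those decisions are intended.

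Two things are at stake. For impetigo, a favourable declaration could mean anything from a modest loss of effect to no effect at all, depending on how common impetigo is. For scabies at 24 months, the same sentence carries over a change score whose variance is dominated by baseline spread between villages. The decision could then fail for reasons unrelated to the regimens.

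**Working it through.** **The plan's own figure.** From the Sample size section: 10 villages per group, true difference 6 − 3 = 3 points, margin 5 points, SDs 2% and 1%, power 80%.
- Pooled SD = √[(2² + 1²)/2] = 1.58 points; SE = 1.58 × √(2/10) = 0.707 points.
- Power = Φ[(5 − 3)/0.707 − 1.96] = Φ(0.87) = 0.81.

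The stated 80% reproduces as a comparison of 12-month scabies prevalence, with the stated SDs taken as the whole village-level SD. It involves neither impetigo nor 24 months.

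**What 5 points means as a share of the two-dose effect.** Impetigo prevalence is not in the article, so the impetigo rows are assumptions.

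| Outcome | Baseline | Two-dose follow-up | Effect | 5 points as share |
|---|---|---|---|---|
| Scabies, 12 months (plan) | 20% | 3% | 17 | 29% |
| Impetigo (assumed) | 5% | 1% | 4 | 125% |
| Impetigo (assumed) | 10% | 2% | 8 | 63% |
| Impetigo (assumed) | 25% | 5% | 20 | 25% |

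In the second row a one-dose regimen with no benefit differs from two doses by 5 − 1 = 4 points, which is inside the margin.

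**Lying inside the margin is not the same as passing.** The upper confidence limit must also be at most 5. Take change as follow-up minus baseline, so that a positive difference is worse for one dose. Assume a baseline village SD of a quarter of the mean, a follow-up SD of a third of the mean, 250 people per village, and no correlation between baseline and follow-up.
- Variance of change, one dose (5% to 5%): 0.0125² + 0.0167² + 2 × 0.05 × 0.95/250 = 0.00081.
- Variance of change, two doses (5% to 1%): 0.0125² + 0.0033² + 0.05 × 0.95/250 + 0.01 × 0.99/250 = 0.00040.
- SE = √[(0.00081 + 0.00040)/10] = 1.10 points; half-width = 2.101 × 1.10 = 2.3 points.
- The no-benefit regimen passes about 14% of the time.
- A one-dose regimen reaching 3%, which loses 2 of the 4 points gained (half the effect), passes about 83% of the time in simulation under the same SD assumptions.
- At baseline 10% and two-dose 2%, a one-dose regimen at 6% (threefold) passes only about 8.5% of the time.

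**Scabies at 24 months.** Use the plan's baseline of 20% (SD 5%). Assume 3% (SD 1%) in both groups at 24 months, with 250 people per village.
- Variance of change, baseline and follow-up uncorrelated: 0.05² + 0.01² + 0.2 × 0.8/250 + 0.03 × 0.97/250 = 0.00336; SD = 5.79 points.
- SE = 5.79 × √(2/10) = 2.59 points; half-width = 2.101 × 2.59 = 5.4 points.
- With correlation 0.5, the variance falls by 2 × 0.5 × 0.05 × 0.01 = 0.0005 to 0.00286; SE = 2.39 points; half-width = 5.0 points.
- Chance that equal regimens meet the rule = P(noncentral t on 18 df ≥ 2.101), with noncentrality 5/SE. With 5/2.59 = 1.93 this is about 45%; with 5/2.39 = 2.09 it is about 51%. Even at correlation 1 it is only about 59%.

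**The same scenario, adjusted for baseline.** The variance of follow-up prevalence alone is 0.01² + 0.03 × 0.97/250 = 0.000216. SE = √(0.000216 × 2/10) = 0.66 points, and the half-width on 17 df is 2.110 × 0.66 = 1.4 points. With correlation 0.5 it is about 1.3 points.

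**The case against.** The best defence is that the sentence carries over only the computation: village prevalence, change, difference of means and confidence interval. Table 1 and the Aims reserve non-inferiority for the primary objective, and no margin is named for the secondary outcomes. That reading is reasonable, and the text does not establish that three further declarations are planned. But the decision rule is part of the analysis that the sentence points to, and nothing excludes it. The change score carries over on either reading.

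A second defence is that an impetigo margin and its expected prevalence belong in the full protocol or analysis plan. Their absence from an article is indeed no fault. The point rests on what the article states: a rule whose literal reach exceeds the definition of its margin.

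Stronger readings that a reader might infer are not supported:
- *The rule would readily pass a regimen several times worse.* This needs two-dose impetigo of about 1% to 2%, which is assumed. Even then, under the change score, a threefold prevalence at two-dose 1% passes 83% of the time at baseline 5% but 49% at baseline 10% and 20% at baseline 20%. A large ratio at low prevalence also applies to the primary margin (3% against 8%), so it is not peculiar to the secondary outcomes.
- *The margin has no basis at 24 months.* The condition and scale are the same as for the primary outcome. Only a reason for the later time point is not given, and the rule there is more likely to be uninformative than lax.
- *The Discussion concedes the point.* Its remark, "A greater or lesser margin may be considered non-inferior in other settings, depending on factors, including baseline disease prevalence", concerns other settings, not other outcomes in this trial. It supports the reasoning only by analogy.

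**Conclusion.** The point holds as a mismatch between the stated reach of the analysis and the defined reach of the margin. It concerns secondary outcomes; the choice of margin for scabies at 12 months is not in question here.

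For impetigo, 5 points could be 25% of the two-dose effect or more than all of it over the assumed range, so a declaration could not be interpreted without a justified margin. The article does not show that 5 points is wrong for impetigo; it does not show that it is suitable.

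For scabies at 24 months the difficulty is precision. A half-width of about 5 points means that two identical regimens would meet the rule about half the time. This rests on the plan's baseline mean and SD, on an assumed 3% in both groups, and on a baseline-to-follow-up correlation between 0 and 0.5.

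**What to change.** Replace the sentence in Secondary outcomes with two statements:
1. The 5% margin and the non-inferiority declaration apply only to scabies at 12 months. Alternatively, set and justify a separate margin for impetigo before the follow-up data are seen. Trial status reports that baseline collection is complete, so the baseline impetigo prevalence needed for this should be available to the sponsor. If 12-month results have already been seen, only the first option remains credible for that time point.
2. For impetigo at 12 and 24 months and scabies at 24 months, report the one-dose minus two-dose difference in village-level follow-up prevalence, adjusted for village baseline prevalence, with its 95% confidence interval.

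No new data are needed. The costs are one degree of freedom for the baseline term (18 to 17) and, under the first option, no formal non-inferiority claim on the secondary outcomes. In the 24-month scabies scenario the gain is a half-width of about 1.3 to 1.4 points instead of about 5.
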